### Recruitment

A target sample size of *N* = 300 will be recruited. [name] research team will oversee online data recruitment and collection. A variety of methods will be used to recruit potential participants. [name] will recruit from cities across Canada and the USA using online ads (e.g. Google Ads, Craigslist, Kijiji, and local news websites), local avenues (i.e. newspapers), and governmental organizations (i.e. Manitoba Liquor & Lotteries). Given the high rates of problem gambling and tobacco smoking in Canada and the USA [7–9, 12], it should be feasible to recruit the required sample size.

Another very important issue will be to recruit a sufficient number of women to be able to examine gender differences in treatment effects. Based on the literature, about one-third of individuals with problem gambling from the community will be women [64]. We will make every effort to ensure that at least one-third of our final sample is comprised of women, although we will aim for a higher percentage during the recruitment process. Inclusive recruitment will ensure that both genders equally contribute to and benefit from the intervention. This is very important, since data show that women are drastically underrepresented in gambling treatment settings. To illustrate, only 2–7% of those who attend Gambler’s Anonymous are women [65]. We aim to greatly improve these numbers for our trial.

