**Methods:**

The aim of this two-arm open-label randomized controlled trial is to examine the effectiveness of an online, self-guided integrated treatment for problem gambling and tobacco smoking. A target sample of 214 participants will be recruited and be randomized into either an 8-week integrated or gambling only control condition. Both conditions will consist of seven online modules following cognitive behavioural therapy and motivational interviewing principles. Our three primary outcomes are (1) the number of days gambled, (2) money spent on gambling activities, and (3) time spent in gambling activities. Secondary outcomes include gambling disorder symptoms, cigarette use, and nicotine dependence symptoms. Assessments will be completed at baseline, at completion (i.e. 8 weeks from baseline), and at follow-up (i.e. 24 weeks from baseline). Generalized linear mixed modelling will be used to evaluate our primary and secondary outcomes. We expect that participants receiving online integrated treatment will show larger reductions in gambling relative to those receiving a control gambling only intervention. We further hypothesize that reductions in smoking will mediate these group differences.

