### Sample-size justification and statistical plan

A meta-analysis showed that CBT/MI (relative to control) treatments have medium effects on gambling [17]. However, we will be comparing two active treatments, which may result in smaller effect sizes. Accordingly, we used G*Power to calculate the sample size needed to detect a small effect size for our primary outcome. We used a 2 (between subjects; treatment condition) by 3 (within subjects; time) mixed design. Assuming a power rate of .80, an *α* of .05, and a correlation of .50 between repeated measures, the required sample size to detect a small effect size is *N* = 164. Given an average attrition rate of 30% in gambling treatment studies [17], our final adjusted sample size is *N* = 214. Generalized mixed modelling will be used to evaluate the main hypothesis that integrated online treatment will result in the larger reductions in gambling than the gambling only treatment. Primary and secondary outcomes will be tested sequentially. We will include all randomized participants in analyses (i.e. intent-to-treat). Missing data will be accounted for using full information maximum likelihood estimation. We will include some covariates in our models if needed. Relevant covariates may include history of psychological treatment, age, gender, and baseline severity of gaming and smoking behaviours. Of particular relevance, we expect variability in adherence to NRT; therefore, we will explore whether NRT use (e.g., # of days patch was used during treatment) affects primary/secondary treatment outcomes.

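### The Recruitment section targets 300 participants, while the abstract and the sample-size section target 214; only 214 has a derivation, so planned enrolment and power are ambiguous.

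*Protocol article*

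**What the plan says.** Three places in the protocol article give a target sample.

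- Recruitment: "A target sample size of *N* = 300 will be recruited". The same paragraph ends by saying that "it should be feasible to recruit the required sample size".
- Abstract, Methods: "A target sample of 214 participants will be recruited and be randomized into either an 8-week integrated or gambling only control condition".
- Sample-size justification and statistical plan: "the required sample size to detect a small effect size is *N* = 164", and after an allowance for 30% attrition, "our final adjusted sample size is *N* = 214".

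The sample-size section gives the basis for its figure: "We used a 2 (between subjects; treatment condition) by 3 (within subjects; time) mixed design", with these settings: "Assuming a power rate of .80, an *α* of .05, and a correlation of .50 between repeated measures". The effect is described only as small, with no number.

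Three other sections bear on the point. The monitoring section says that no interim analyses are intended and that no stopping guidelines exist. Trial status gives 31 December 2020 as the estimated end of recruitment. The sample-size section plans to analyse everyone randomised, handling missing data by full information maximum likelihood.

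**The concern.** The abstract and the Recruitment section both name a target sample and both say that it will be recruited, yet the numbers are 214 and 300. All three statements are current text. Nothing in the visible article presents 300 as a later increase, as a number to be screened, or as the result of a calculation.

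The target sample size fixes how many people are randomised and what power the comparison has. With two values, a reader cannot tell which power the investigators planned for, and a later report could not say whether the trial met its target: 250 randomised would exceed one figure and fall short of the other. A separate analysis plan would not settle this, because the article does not omit the target but states it twice with different values.

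**Working it through.** **Inputs from the sample-size section.** Two groups (k = 2), three time points (m = 3), correlation between repeated measures ρ = 0.50, α = 0.05, power 0.80, 30% attrition.

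**Assumptions.** Cohen's f = 0.10 for the small effect, 1:1 allocation and sphericity = 1. The article states none of these, but together they return its own figure exactly.

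**Step 1: reproduce 164.** For the within-between interaction in a repeated-measures ANOVA, the noncentral F test has λ = f² × N × m / (1 − ρ), df1 = (k − 1)(m − 1) and df2 = (N − k)(m − 1). With N = 164:

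- λ = 0.01 × 164 × 3 / 0.50 = 9.84
- df1 = 2, df2 = 162 × 2 = 324
- power = 0.805

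164 is the smallest even N that reaches 0.80, so the stated figure is reproduced. A between-subjects main effect under the same inputs would need 526, so that is not the test behind 164.

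**Step 2: reproduce 214.** 164 × 1.30 = 213.2, rounded up to 214. This is the stated figure. Dividing by the proportion retained gives 164 / 0.70 = 234.3, rounded up to 235.

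**Step 3: look for a route to 300.**

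| Route | Result |
|---|---|
| 164 × 1.30 | 214 |
| 164 / 0.70 | 235 |
| 214 × 1.30 (attrition counted twice) | 279 |
| 214 / 0.70 (attrition counted twice) | 306 |

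None gives 300. Working backwards, 300 randomised with 164 completers implies a loss of 1 − 164/300 = 45.3%. The sample-size section does not use that rate. The wider dropout ranges quoted elsewhere (14 to 50% in the Background, 21 to 80% under Attrition) are not adopted for planning. The gap between the targets is 300 − 214 = 86, and 86 / 214 = 40%.

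**Step 4: power under each target**, same formula and f = 0.10.

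| Randomised | Completers at 30% loss | Power, completers only | Power if nothing were lost |
|---|---|---|---|
| 214 | 150 | 0.77 | 0.90 |
| 235 | 164 | 0.80 | 0.93 |
| 300 | 210 | 0.90 | 0.97 |

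The last two columns bracket what a likelihood analysis of all randomised participants could achieve. It uses the partial data of those who drop out, so it should lie between them.

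**The case against.** **300 may be a screening figure.** This is the best defence. The Recruitment section speaks of potential participants and separately of a final sample. Under Informed consent and randomization, people consent, register and complete baseline before eligibility is decided. Ineligible people may receive the intervention but are left out of the study. The trial schematic (Fig. 1) is also not available in the text reviewed. The phrase about the required sample size, some sentences after 300, need not refer to 300, since the sample-size section attaches those words to 164. So the screening reading cannot be excluded. But no visible text states it: the Recruitment section calls 300 a target sample size, and the abstract says that the 214 are both recruited and randomised. If screening was meant, the article needs to say so.

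**The completer figures are conservative.** This stands. The planned analysis keeps all randomised participants, so 0.77 and 0.90 are lower values rather than forecasts. The difference between the targets remains under either column. The larger target would also raise power, so the contradiction does not by itself make the trial underpowered. The figure of 0.77 comes from how 164 was inflated to 214, which is a separate matter from the existence of two targets.

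**A reader might infer that two targets allow recruitment to stop between 214 and 300 according to the results.** The documents do not support this. The monitoring section disclaims interim analyses, no section says that outcomes by arm are viewed during recruitment, and the open-label status described concerns participants and the support person. An estimated closing date is given.

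**A reader might also infer that power cannot be stated at all.** It can be stated for each target, as above. What is unclear is which target applies.

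**Conclusion.** Wrong as written: an internal inconsistency in a core design figure. The Recruitment section's 300 conflicts with 214 in the abstract and the sample-size section, by 86 participants or 40% of 214. Only 214 has a derivation, and 300 does not follow from 164 with 30% attrition by either formula. Planned power is therefore ambiguous between about 0.77 and 0.90 on a completer basis.

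The contradiction can be read directly from the text and needs no assumption. The power figures rest on f = 0.10, 1:1 allocation, sphericity and a completers-only count. The first three are supported by their exact return of 164; the last is deliberately cautious. The conclusion does not extend to outcome-driven stopping, which the documents do not show to be planned.

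**What to change.** State one randomised-sample target in the abstract, the Recruitment section and the sample-size section, with the attrition assumption actually used to reach it.

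- If 300 is the number to be screened or consented, label it so and keep the randomised target separate.
- If 300 is the randomised target, give the reasoning that was in fact used. The 45% loss computed above is only a back-calculation and should not be adopted as the rationale after the event.
- If 214 is kept, restate the power it delivers after 30% loss (about 0.77 on completers at f = 0.10), with whatever recovery is expected from the likelihood analysis. Retaining 164 completers needs 235.

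Add one sentence saying that enrolment ends at the stated number or at the closing date, whichever comes first, without reference to outcomes by arm. This is an ordinary safeguard and agrees with the monitoring section's statement that no interim analyses are intended.

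The cost is a wording correction in three places and a check that the registry entry and consent form carry the same number, since Trial status names these as the places where modifications are posted. No participants are needed beyond a target already written, as 235 lies below 300.

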### Inclusion criteria

Our main target demographic will be adults with moderate levels of gambling problems who identify as daily smokers. Inclusion criteria will include (1) ages 19+, (2) problem gambling status based on reporting a score of > 3 on the Problem Gambling Severity Index (PGSI), (3) reporting current daily smoking, (4) fluency in English, and (5) have weekly Internet access.

### Exclusion criteria

Exclusion criteria will include (1) self-reported current engagement in other psychosocial treatments for problem gambling and/or smoking, (2) elevated suicidality (scoring greater than “minimal risk” on the P4 suicide screener) [66], (3) past-90-day psychosis or mania, and (4) presence of a severe substance use disorder (SUD). SUD severity will be determined based on established cut-offs on widely used and validated screening measures for alcohol and other drug use. For alcohol, individuals with a score of > 20 on the Alcohol Use Disorder Identification Test (AUDIT) [67] will be excluded from the study. For other substance use, individuals with a score of > 5 on the Drug Abuse Screening Test-10 (DAST-10) [68] will be excluded. The rationale for excluding those with severe SUDs is based on the large literature showing that these individuals need intensive residential treatments (with corresponding medical supervision) [69] and hence would not benefit from self-guided online interventions, such as the one to be provided in the current study. We will provide a list of local addiction and financial resources for those with severe AUD and SUD symptoms.

### Sample-size justification and statistical plan

A meta-analysis showed that CBT/MI (relative to control) treatments have medium effects on gambling [17]. However, we will be comparing two active treatments, which may result in smaller effect sizes. Accordingly, we used G*Power to calculate the sample size needed to detect a small effect size for our primary outcome. We used a 2 (between subjects; treatment condition) by 3 (within subjects; time) mixed design. Assuming a power rate of .80, an *α* of .05, and a correlation of .50 between repeated measures, the required sample size to detect a small effect size is *N* = 164. Given an average attrition rate of 30% in gambling treatment studies [17], our final adjusted sample size is *N* = 214. Generalized mixed modelling will be used to evaluate the main hypothesis that integrated online treatment will result in the larger reductions in gambling than the gambling only treatment. Primary and secondary outcomes will be tested sequentially. We will include all randomized participants in analyses (i.e. intent-to-treat). Missing data will be accounted for using full information maximum likelihood estimation. We will include some covariates in our models if needed. Relevant covariates may include history of psychological treatment, age, gender, and baseline severity of gaming and smoking behaviours. Of particular relevance, we expect variability in adherence to NRT; therefore, we will explore whether NRT use (e.g., # of days patch was used during treatment) affects primary/secondary treatment outcomes.

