### Existing evidence-based treatments for problem gambling

Existing evidence-based treatment protocols for problem gambling generally combine strategies from two main psychological intervention frameworks: CBT and MI [17, 38]. CBT is a structured and goal-oriented treatment, where individuals acquire skills to reduce problem gambling through modifying thoughts and behaviours in response to internal (e.g. negative emotions) and external (e.g. gambling cues) triggers. During CBT, individuals with gambling problems strengthen coping skills by completing various exercises both in-session and at home between sessions. Complementing CBT, MI strategies are used in gambling treatment to elicit and motivate positive change. MI is a patient-centred and collaborative approach, where the goal is to help patients resolve ambivalence about change and get them to move in a direction that is consistent with personal values. MI is typically a prelude to CBT, but also a style that a therapist can return to if barriers are encountered during CBT. The weight of the evidence demonstrates that the combination of CBT and MI has synergistic beneficial effects on gambling and smoking behaviours during treatment [17–19, 21, 38]. By increasing motivation for change using MI, individuals with problem gambling may be more willing to engage in the effortful activities of CBT (e.g. homework), which in turn, are essential for building better coping skills. Integrated MI may also help to clarify a problem gambler’s core values in CBT by creating a discrepancy between current and desired behaviour. Thus, from a theoretical perspective, CBT and MI naturally complement each other in the treatment of problem gambling. Supporting this, a recent meta-analysis showed that CBT/MI treatments reduce problem gambling symptoms with medium effect sizes [17], and online CBT treatments reduce problem gambling amount, frequency, and urges [39].

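### N = 164 gives 80% power for an interaction of f = 0.10, which is a between-arm difference of about 0.42 to 0.49 SD and not a small between-arm difference

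*Protocol article*

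**What the plan says.** Under *Sample-size justification and statistical plan*, the article starts from medium effects of CBT/MI against control; the Background says likewise that "CBT/MI treatments reduce problem gambling symptoms with medium effect sizes". It then notes that "we will be comparing two active treatments, which may result in smaller effect sizes", and for that reason "we used G*Power to calculate the sample size needed to detect a small effect size for our primary outcome".

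The design entered was as follows: "We used a 2 (between subjects; treatment condition) by 3 (within subjects; time) mixed design". The other inputs were: "Assuming a power rate of .80, an *α* of .05, and a correlation of .50 between repeated measures". The result is that "the required sample size to detect a small effect size is *N* = 164", followed by an allowance for dropout: "Given an average attrition rate of 30% in gambling treatment studies [17], our final adjusted sample size is *N* = 214".

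The article gives no numerical effect size, no effect-size metric, and no difference in days, dollars or minutes gambled.

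**The concern.** The argument moves from a treatment-versus-control effect to a smaller effect between two active arms. Both are differences between arms, so a reader will take the small effect to be a small between-arm difference. The calculation, however, appears to use Cohen's f for a group-by-time interaction, and small on that scale is not small as a between-arm difference.

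At stake is what the trial can be said to detect. If the reduction from medium to small was made only in the label, the stated sensitivity is too favourable, and a non-significant result could be given more weight against a modest added benefit than the data would bear.

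**Working it through.** **Inputs.** From the article: 2 groups, m = 3 times, power .80, alpha .05, correlation rho = .50, N = 164. Assumed: 1:1 allocation and sphericity. Inferred: f = 0.10.

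**Step 1: reproduce 164.** For the interaction in a repeated-measures ANOVA, lambda = f² × N × m / (1 − rho), with df = 2 and 2(N − 2).
- At f = 0.10 and N = 164: lambda = 0.01 × 164 × 3 / 0.5 = 9.84, df = 2 and 324, power 0.805.
- At N = 162, power is 0.7998, so 164 is the smallest even N that reaches .80.
- Solving for f at N = 164 and power .80 gives 0.0994.
- Of the other variants tried at f = 0.10, the between-group main effect needs 526, and two alternative noncentrality definitions need 486 and 966. The within-subject time effect also gives 164, but it does not compare the arms.

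**Step 2: convert f to a between-arm difference.** Let d_t be the between-arm difference at time t in SD units, zero at baseline because of randomisation. Then f² = mean over time of ((d_t − mean d)/2)².
- Sustained (0, d, d): f² = d²/18, so f = 0.10 gives d = 0.10 × √18 = 0.424.
- Linear over assessments (0, d/2, d): f² = d²/24, so d = 0.10 × √24 = 0.490.
- Linear in weeks (0, d/3, d): d = 0.481.

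A simulation of 4,000 trials at N = 164 gave power of 80.4% for 0.424 sustained and 80.6% for 0.49 linear.

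**Step 3: power of the interaction test at 0.20 SD** (an assumed meaning of small on the difference scale). At N = 164, lambda = (0.04/18) × 984 = 2.19 sustained and (0.04/24) × 984 = 1.64 linear, where 984 = 164 × 3 / 0.5.

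| Analysed N | Sustained | Linear |
|---|---|---|
| 150 | 0.224 | 0.177 |
| 164 | 0.241 | 0.190 |
| 214 | 0.306 | 0.237 |
| 300 | 0.414 | 0.320 |

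Here 150 is what 30% attrition leaves of 214 (214 × 0.70 = 149.8), and 300 is the target given under *Recruitment*. Simulation at 164 gave 23.7% and 18.9%. Reaching 80% at 0.20 SD would take 726 (sustained) or 966 (linear) analysed.

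**Step 4: a more efficient analysis.** Take the mean of the 8- and 24-week values, adjusted for baseline. Its residual variance is (1 + .5)/2 − .5² = 0.50, so SD = 0.707.
- With 82 per arm, SE = 0.707 × √(2/82) = 0.110. The difference with 80% power is (1.960 + 0.842) × 0.110 = 0.31 SD. Power at a sustained 0.20 SD is 0.44.
- With 75 per arm, the corresponding figures are 0.32 SD and 0.41.
- Power at 0.20 SD is 0.54 with 214 analysed and 0.69 with 300.

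**The case against.** The case for the protocol is substantial, and most of it stands.

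- **Not an arithmetic error.** A reader might infer that 164 is miscalculated or that the power statement is untrue. The article supports neither: 164 is exactly right for f = 0.10, which is the usual small value on the f scale, and the article never says 0.20 SD. That benchmark is introduced here.
- **No blanket 20–25% power.** The interaction figures belong to an unadjusted 2-df test. The article plans generalized mixed modelling on all randomised participants with full information maximum likelihood, and allows baseline severity as a covariate if needed. Step 4 shows that such an analysis could do clearly better. Even so, no analysis examined reaches 80% at 0.20 SD, even with 300 analysed.
- **Medium is not quantified.** A reader might conclude that the trial is sized for the same effect as that seen against control. The article gives neither the metric nor the value behind medium, and elsewhere in the Background calls effects from the same cited source modest. That 0.42–0.49 SD lies near a conventional medium of 0.5 is an assumption about convention.
- **Misreading of a null result.** Nothing in the article says that a non-significant result will be taken to exclude a small benefit, and the study is described as a pilot with larger trials to follow. That harm is a risk and not a stated plan. The pilot label does not remove the need for accuracy, since the article makes a formal 80% power claim.

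**Conclusion.** The point holds as a matter of effect-size scale and should be fixed. The calculation is correct for a group-by-time interaction of f = 0.10, but it does not provide 80% power for a small difference between the arms, which is what the preceding reasoning leads a reader to expect. On the interaction test, 80% power at N = 164 needs about 0.42 SD (sustained) to 0.49 SD (linear). With baseline adjustment and averaging over the two post-baseline assessments, the figure falls to about 0.31 SD with 164 analysed and 0.32 SD with 150.

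This rests on f = 0.10 being the value entered, equal expected baselines, a common SD, rho = .50, sphericity and 1:1 allocation. The power figures at 0.20 SD rest also on reading small as 0.20 SD; the 0.42–0.49 SD range does not.

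**What to change.** 1. Replace the phrase about a small effect size with: *a group-by-time interaction of f = 0.10, i.e. a between-arm difference of about 0.42 SD (sustained at T1 and T2) to 0.49 SD (linear), assuming equal baselines, a common SD, rho = .50 and sphericity*. The authors should confirm f and the tested term from their G*Power record.
2. State that power for a difference of 0.20 SD is well below 80%, giving the figure for the model and covariates actually planned. A single blanket percentage taken from the unadjusted interaction test should not be used.
3. Add that a non-significant result will be interpreted from the confidence interval for the between-arm difference and not as absence of a small benefit.

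The cost is a few sentences and a less favourable statement of sensitivity. Design, analysis and number of participants are unchanged.

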## Methods/design

### Design

This open-label pilot project will consist of a two-arm RCT (Clinicaltrials.gov ID NCT03614884; see Figs. 1 and 2 for an overview). [name] and his research team will collect the data in Canada and the USA. Participants will be randomly assigned into one of two conditions. In the experimental condition, participants will receive an 8-week online integrated intervention for problem gambling and smoking. In the control condition, participants will receive a similar 8-week online intervention for problem gambling without treatment content to address smoking. Online assessments will occur before randomization (T0; baseline), at 8 weeks since baseline (T1; treatment end), and at 24 weeks since baseline (T2; follow-up; see Table 1). The timeline of these assessments, including the longer-term follow-up, is consistent with previous RCTs examining technology-based interventions for problem gambling and those for smoking cessation [62, 63]. Participants will be compensated based on the following schedule: $20 per assessment, a bonus of $20 for completing all three assessments, and $20 for completing at least five of the treatment modules (max compensation per participant = $100). For ethical reasons, participants will be compensated in the form of gift cards to Amazon.ca. This RCT is registered with ClinicalTrials.gov for transparency and to avoid publication bias. Prior to the initiation of the study, we obtained ethical approval from the Research Ethics Board (REB) at the University of Manitoba (#P2018:088 HS22037) and York University (ES2020-006).

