#### Attrition

Intervention studies show substantial variability in attrition rates, depending on treatment orientation, clinical severity, and so forth [17]. Generally, dropout rates are high in populations with behavioural and substance use addictions—ranging from 21 to 80% [84]. We are aware of this possible influence on attrition. Regular contact will be provided via automated emails and, if a participant prefers, phone to provide personalized support that is not typical of online interventions. It has been shown that automated and personalized support in self-guided interventions can improve treatment adherence and reduce attrition [85]. This may reduce dropout. Finally, we will offer participants the possibility to receive a personalized feedback report at the end of the study. This report will contain information about their treatment progress. The combined use of the strategies above will help reduce the attrition rate.

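### The 30% attrition allowance was added as 164 × 1.30 = 214 instead of 164 / 0.70 = 235, so 214 keeps the required 164 completers only if attrition stays at or below 23.4%

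*Protocol article*

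**What the plan says.** All the inputs stand in the protocol article under *Sample-size justification and statistical plan*.

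- Target effect: "we used G*Power to calculate the sample size needed to detect a small effect size for our primary outcome". No numerical effect size is given.
- Design: "We used a 2 (between subjects; treatment condition) by 3 (within subjects; time) mixed design".
- Parameters: "Assuming a power rate of .80, an *α* of .05, and a correlation of .50 between repeated measures".
- Result: "the required sample size to detect a small effect size is *N* = 164".
- Attrition step: "Given an average attrition rate of 30% in gambling treatment studies [17], our final adjusted sample size is *N* = 214".

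The same section plans to analyse everyone randomized, using generalized mixed modelling with full information maximum likelihood for missing data.

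The abstract repeats the adjusted figure: "A target sample of 214 participants will be recruited and be randomized". The *Recruitment* section under Methods/design instead gives a target of 300 and does not derive it.

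**The concern.** An attrition rate is a proportion of the people enrolled. To end with a required number after losing 30% of those enrolled, that number is divided by the retained share, 0.70. Adding 30% of the required number applies the rate to the smaller base and gives too few people. The stated 214 matches the second operation and not the first.

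At stake is the article's only derived sample size, which the abstract presents as the recruitment target. A reader will take 214 to mean that the trial can lose 30% of participants and still have the 164 on which its 80% power was calculated. It cannot.

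**Working it through.** **Inputs from the article.** Required N = 164; attrition 30%; adjusted N = 214; two groups (k = 2); three time points (m = 3); correlation ρ = 0.50; α = 0.05; target power 0.80.

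**Assumptions.** Small effect taken as Cohen's f = 0.10, because the article gives no number. Equal allocation, because the article says only "Participants will be randomly assigned into one of two conditions". Neither affects steps 2 and 3, apart from rounding 235 up to 236 for equal arms.

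**Step 1. Reproduce 164.** For the group-by-time interaction in a repeated-measures F test:

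- λ = f² × N × m / (1 − ρ)
- df1 = (k − 1)(m − 1) = 2
- df2 = (N − k)(m − 1)

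At N = 164, λ = 0.01 × 164 × 3 / 0.5 = 9.84 and df2 = 324, giving power 0.805. The smallest N reaching 0.80 is 163, or 164 with equal arms. The stated figure is reproduced, which supports f = 0.10.

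**Step 2. Reproduce 214.**

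- 164 × (1 + 0.30) = 213.2, rounded up to **214**. This matches.
- 164 / (1 − 0.30) = 234.3, rounded up to **235** (236 for equal arms). This does not match.

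**Step 3. What 214 delivers.**

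- Completers at 30% attrition: 214 × 0.70 = 149.8, about 150. Shortfall: 164 − 150 = 14.
- Largest attrition that still leaves 164: 1 − 164/214 = 23.4%.
- Check on the corrected figures: 235 × 0.70 = 164.5 and 236 × 0.70 = 165.2.

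**Step 4. Power on the article's complete-data basis.** At N = 150, λ = 0.01 × 150 × 3 / 0.5 = 9.00 and df2 = 296, giving power **0.766**, against 0.805 at 164.

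**Step 5. Power at N = 214 under a likelihood-based mixed model.** Further assumptions, none of them stated in the article: compound symmetry with ρ = 0.50, baseline observed for all, data missing at random, 30% missing at week 24, and an effect scaled so that 164 complete cases give 0.805.

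| Between-arm effect | All dropouts leave before week 8 | Half before week 8, half after | All after week 8 |
|---|---|---|---|
| Present at week 8, sustained | 0.81 | 0.85 | 0.88 |
| Linear growth to week 24 | 0.80 | 0.81 | 0.82 |
| Present at week 8, half lost by week 24 | 0.80 | 0.86 | 0.90 |
| Week 8 only | 0.78 | 0.84 | 0.88 |
| Week 24 only | 0.78 | 0.78 | 0.78 |

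The range is about 0.78 to 0.90.

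**Step 6. The other target.** With 300 enrolled, 30% attrition leaves 300 × 0.70 = 210 completers and power of about 0.896 by the step 1 formula.

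**The case against.** The strongest objection is that the trial does not plan a completer analysis. All randomized participants enter a mixed model fitted by full information maximum likelihood, so people who drop out still contribute what they provided. A reader might infer from the slip that the trial misses 80% power. The article does not support that: in step 5 power at 214 is at or above 80% in most of the patterns tried, and the worst is about two points short. This part of the objection stands, and the 77% must always be labelled as a completer figure. It does not rescue 214, however. The article took a complete-data sample size and inflated it for attrition, which counts dropouts as lost. By that reasoning the answer is 235. Relying on partial data would be a different justification, and the article does not offer it.

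A second objection is that the recruitment target of 300 exceeds 235, so the slip would have no practical effect if 300 is the working figure. That is correct as far as it goes. But 300 is not derived and conflicts with both places that say 214, so it cannot be read as a silent correction.

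Third, the *Attrition* section of the Discussion says that "dropout rates are high in populations with behavioural and substance use addictions—ranging from 21 to 80" per cent, and a reader might be tempted to calculate much lower power from the upper end. That range describes addiction populations in general. The trial is sized on 30%, and losses beyond that would not be a consequence of this arithmetic slip.

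Finally, the gap is modest and the article calls the trial a pilot. Both are true, and they bear on how much the error matters, not on whether the figure is right.

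**Conclusion.** The attrition adjustment is wrong as written. The size consistent with 164 and 30% attrition is 235 (236 for equal arms), so the stated figure is 235 − 214 = 21 participants too low. At the planned attrition 214 leaves about 150 completers, and it keeps 164 only up to 23.4% attrition. These results use only the article's own numbers.

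The effect on power is limited and depends on the analysis. On the complete-data basis that the article used, and with f = 0.10 assumed, it is 76.6% instead of 80%. Under the planned intention-to-treat likelihood analysis the loss may be small or absent, at about 78% to 90% under the assumptions in step 5. The defect is therefore a misstated sample-size figure, repeated in the abstract. It is not a demonstration that the trial is underpowered. No hypothesis, test, error rate or analysis set is affected.

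**What to change.** In *Sample-size justification and statistical plan*, do one of the following:

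1. State the attrition-adjusted size as 235, or 236 for 1:1 allocation.
2. Keep 214 and say that it tolerates 23% attrition. Any power quoted at 30% attrition (about 77%) must be labelled as on a completer basis.
3. Keep 214 and justify it by a power calculation for the planned mixed model, stating the assumed dropout timing and effect pattern.

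Whichever is chosen, give the numerical effect size behind the word small, and use a single target in the abstract, the *Recruitment* section and the sample-size section. That means reconciling 214 with 300. If 300 is the working target, say so and explain it; it already covers 235.

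Options 2 and 3 cost wording and, for option 3, a short calculation. Option 1 adds 21 or 22 participants to the stated 214, and none if recruitment is in fact aiming for 300.
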